#### AT Group

Following the baseline assessment and brief advice to quit video, participants in AT will be given a 10-week supply of nicotine patches and lozenges (equivalent to ST). After randomization, they will be sent an email with a link to the smartphone app and instructions on how to use the app. AT will include (1) 12 proactive treatment videos (delivered weekly) that will be tailored to smoking status, motivation, agency, and negative affect or stress; (2) 26 weeks of on-demand access to treatment content; and (3) 26 weeks of text content.

As with participants in the ST group, AT participants will complete weekly 4-item smoking status, self-efficacy, motivation, and stress assessments for 26 weeks. An algorithm will use responses to these assessments to deliver brief, 2- to 6-minute, videos from an existing library of tailored content. Weekly topics are listed in Table 2. The AT app will deliver the most appropriate video each week, specifically tailored for each participant. During the first 12 weeks, videos will be proactively launched each week following the completion of the assessment. Throughout the entire 26-week treatment period, participants will also have the option to self-initiate treatment sessions. In addition, referrals to extra treatment resources will be available through the app. Resources will include phone numbers to substance abuse treatment centers, psychiatric services, HIV case management, and other services (eg, housing needs).

**Table 2 table2:** Automated treatment session topic by study week.

Study week	Topic
Week 1	Preparing to quit
Week 2	Quit day
Week 3	What to do if you have a cigarette
Week 4	Nicotine patches and lozenges
Week 5	Smoking, stress, and mood
Week 6	Health benefits of quitting
Week 7	Smoking and your weight
Week 8	Staying on track
Week 9	Financial benefits of being a nonsmoker
Week 10	Taking care of yourself
Week 11	Social benefits of being a nonsmoker
Week 12	Life without cigarettes

The primary goal of the AT app is to function autonomously. It is designed to require minimal human involvement while being appropriate for implementation in various environments. This approach is expected to perform better than, yet share common mechanisms of action (eg, motivation, agency, and stress or negative affect) with, the behavioral standard of care (ie, quitline counseling). Underlying AT is a platform consisting of both a staff-facing dashboard and a mobile app. Videos were created with Adobe After Effects, an animation software package that is widely used in media campaigns.

On the basis of our prior work, as well as the growing literature supporting the efficacy of text messaging interventions for promoting smoking cessation, participants in the AT group will also receive smartphone-delivered text content [39,94]. This content will be delivered in the form of notifications generated by the app. Daily notifications will begin shortly before the scheduled quit date and continue through month 3. During months 4 to 6, the notification frequency will drop to once per week. The content of these notifications will be designed to target the hypothesized mechanisms and promote NRT adherence. Furthermore, the notifications will encourage participants to access additional on-demand content within the app. Participants will be referred to by first name within the notifications as a way of personalizing the treatment.

### Measures and Assessment Strategy

Several considerations guided our assessment procedures. First, we attempted to include measures with established reliability and validity. If measures with established psychometric properties were not available, measures were required to at least have face validity. Second, assessments had to either (1) represent our hypothesized mechanisms, (2) empirically predict smoking behavior, or (3) describe the sample. Measures were informed by models of health behavior, theories of nicotine dependence, and existing data. To ensure that the study is available to a representative sample of the target population, we will recruit both English- and Spanish-speaking participants. Most of the measures have been translated and validated in Spanish. A certified translator will be used for measures that have not yet been translated.

The REDCap system will be used to administer the surveys. REDCap is a secure web-based app designed to support secure data capture for cleaning, storage, and analysis. Moffitt Cancer Center is a member of the REDCap Consortium.

#### Primary Outcomes

The main outcome is self-reported 7-day abstinence smoking status at the 12-month follow-up. Other definitions of abstinence, such as biochemically verified abstinence using salivary cotinine and self-reported 24-hour, 30-day, and continuous abstinence, will be examined as secondary outcomes. Participants who report 7-day abstinence will be mailed a cotinine kit with instructions for providing the cotinine sample. Study staff will be available by phone and email if participants have questions about the collection process. Participants will be asked to return cotinine samples using a prepaid envelope.

All participants (ST and AT) will complete brief smartphone-delivered assessments each week during the 26-week treatment period. These assessments will be delivered to AT participants through the app, while ST participants will receive their assessments through a REDCap link. Regardless of the treatment group, assessments will be identical and include current smoking status, motivation, agency, and stress or negative affect. Responses to the assessments will be used to select the appropriate treatment content for AT participants, as described above.

#### Assessment of Treatment Engagement–Related Variables in AT

An important focus of our evaluation of AT is to track and examine how frequently participants interact with the app and the duration of these interactions. Thus, each interaction will be date- and timestamped, and we will note how often specific features of the app are used. These data will allow us to examine the frequency and duration of participants’ use of the various components of the app and the specific conditions under which participants engage with the app components. This information will be used to help guide future refinements of the app.

### Data Analysis Plan

Descriptive analyses will be conducted to determine which variables, if any, should be transformed before inferential analyses. In addition, descriptive statistics for demographic, smoking-related, and health-related variables will be used to characterize each sample. The samples will be compared to identify differences despite randomization, which may necessitate inclusion in models testing hypotheses. Descriptive statistics will also be used to summarize the participants’ interactions with the app.

### Primary Aim

The primary aim of this study is to evaluate the efficacy of AT in facilitating smoking cessation among people with HIV. We hypothesize that at 12 months postenrollment, smoking abstinence rates will be higher in the AT group than in the ST group. The primary outcome is self-reported 7-day point prevalence abstinence at 12 months. As is traditional in smoking cessation research, participants who do not complete a follow-up will be coded as smoking. Log-binomial regression will be used, with the intervention group (AT vs ST) as the primary predictor. Variables found to differ by group in preliminary analyses (*P*<.10) will be included as covariates. Differences in treatment effects as a function of sex assigned at birth will also be examined.

Additional analyses will evaluate the effects of the intervention on other definitions of smoking abstinence: biochemically verified abstinence using salivary cotinine and self-reported 24-hour, 30-day, and continuous abstinence. Outcomes from the 3- and 6-month follow-ups will also be considered. Repeated-measures analysis using generalized linear mixed models with a log-link function and the appropriate random-effect covariance structure will be used to analyze outcomes across all assessments with intervention, time, and their interaction as the primary model variables. Model fitting and diagnostics will follow the general approach described by McCullagh and Nelder [113] and McCulloch et al [114], when applicable. Adjustments for multiple comparisons will be made using the methods recommended by Westfall and Young [115].

### Secondary Aim 1

The first secondary aim is to explore the role of potential mediators and moderators. Specifically, we will compare the magnitude of the mediated effects via common mechanisms (ie, motivation, agency, and stress or negative affect) on smoking abstinence between the AT and ST groups. We will also investigate the role of several established HIV-specific moderators (ie, stigma, resilience, disease progression, and HIV symptom burden). Furthermore, exploratory analyses will examine the associations of various AT treatment components with outcomes.

While we hypothesize common mechanisms of AT and ST, it is important to identify the relative strengths and weaknesses of the mechanisms on which each approach relies to facilitate cessation. Participants in ST (vs AT) may report higher levels of quit motivation, whereas those in AT (vs ST) may report higher self-efficacy. Such hypotheses can be tested via mediation analyses with the intervention group (AT vs ST) as the independent variable and smoking abstinence and the hypothesized mechanisms (ie, motivation, agency, and stress or negative affect) as potential mediators. Mediation will be evaluated using approaches developed by MacKinnon [116] and Preacher and Hayes [117-119]. We will also explore the role of HIV-specific moderators (ie, stigma, resilience, disease progression, and HIV-symptom burden) of these indirect effects on the outcome of smoking abstinence.

### Secondary Aim 2

Our second secondary aim is to conduct economic evaluations from a societal perspective as well as a health system perspective to evaluate the cost and cost-effectiveness of AT versus ST. Although the societal perspective is recommended by the Second Panel on Cost-Effectiveness in Health and Medicine [120], we expect that a health system perspective will be of greater interest to decision makers in the public health sector who are responsible for making implementation decisions about smoking cessation programs. Conventional cost-effectiveness analysis will be used to summarize findings in terms of the incremental cost-effectiveness ratio (ICER) [120-122]. The ICER, calculated as the difference in mean costs between new (ie, AT) and ST divided by the difference in mean effectiveness between the two, estimates the additional resources needed to achieve an increase in one unit of effectiveness. We will use 2 commonly used effectiveness measures—number of quitters and years of life saved (YOLS) [123], to compare the ICER with other published cost-effectiveness analyses. The number of quitters in each arm will be retrieved from the 12-month self-reported abstinence assessment. We will extrapolate from abstinence to YOLS using a published algorithm that models YOLS per quitter [124]. The algorithm will be revised using current estimates of age-specific smoking-attributable deaths [125]. We will also include quality-adjusted life-years, which will be calculated based on a measure of health utilities, the EQ-5D-5L [61].

We will also use the net benefit approach [126,127], which transforms the ICER into a net benefit, defined as NB(λ) = λ × ΔE – ΔC, where λ represents the societal willingness to pay, ΔC represents the incremental costs, and ΔE represents the incremental effectiveness. A benefit of the net benefit approach is that it can be incorporated into a regression framework to allow for covariate adjustments and the examination of interaction effects [128].

Moreover, we will assess the short- and long-term economic impact of the interventions. The short-term analysis will use the number of quitters and quality-adjusted life-years as the effectiveness measure and assess cost-effectiveness based on information collected at the 3-, 6-, and 12-month follow-ups. The long-term analysis will extrapolate the intervention effect to lifetime and use YOLS. A 3% discount rate will be applied to costs and outcomes accrued in the second year and forward. We will first perform a deterministic analysis, where point estimates of ICERs or cost differences will be calculated. To obtain the 95% CIs, we will apply nonparametric bootstrapping methods to the person-level data [129]. We will conduct one-way sensitivity analyses to examine the impact of alternative measures of cost and outcomes. We will then apply the Bayesian approach to construct the cost-effectiveness acceptability curve and conduct a probabilistic sensitivity analysis [130,131]. We will conduct Bayesian analysis using WinBUGS (University of Cambridge) or STATA (StataCorp LLC), with costs modeled as a gamma or log-normal distribution and abstinence as a binomial distribution. Finally, we will apply a regression-based cost-effectiveness analysis. Individual-level net benefit will be regressed on covariates, plus a binary variable reflecting AT versus ST. The model will be analyzed using generalized linear mixed models to examine cost-effectiveness over time.

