### Randomization

Following completion of the baseline assessment, the participants will be randomized to the treatment group (ST or AT) using stratified randomization. Sex assigned at birth, HIV disease stage, and nicotine dependence will be balanced.

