### Power Considerations

Because an intention-to-treat approach will be used for our primary analysis, and participants lost to follow-up will be classified as smokers, our power calculation assumes a sample size of 500 (250/500, 50% per group). Power is based on the primary aim of comparing self-reported abstinence rates between AT and ST at the 12-month follow-up [134]. On the basis of findings from our AAC implementation study [24,25], we expect 5% abstinence in ST. Assuming a sample size of 250 per group, a 2-group large-sample normal approximation test of proportions with a 2-sided 0.05 significance level will have 80% power to detect an increase in abstinence of 7% in AT compared with ST. Simulation studies using similar and smaller samples have demonstrated that bootstrap resampling approaches are more powerful than other approaches for estimating indirect effects and conditional indirect effects [135-137]. Therefore, we expect to have sufficient power to detect effects.

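### Primary-model covariates are chosen by P<.10 baseline tests, which select on chance imbalance and almost never admit the three stratification factors; the numerical effect is small and the fix near-free

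*Protocol article*

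**What the plan says.** Under Primary Aim, the outcome is self-reported 7-day abstinence at 12 months, with participants who miss the follow-up counted as smoking. The model is given as: "Log-binomial regression will be used, with the intervention group (AT vs ST) as the primary predictor". Treatment group is the only term fixed in advance. Covariates are then added by a rule: "Variables found to differ by group in preliminary analyses", with P<.10 as the threshold.

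The opening of the Data Analysis Plan shows that the screen compares the randomized groups: "The samples will be compared to identify differences despite randomization, which may necessitate inclusion in models testing hypotheses". That sentence is permissive, whereas the Primary Aim sentence is mandatory. The Data Analysis Plan describes the variables only as broad classes (demographic, smoking-related, health-related); no candidate list is given.

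The Randomization section says that "the participants will be randomized to the treatment group (ST or AT) using stratified randomization", and names the factors: "Sex assigned at birth, HIV disease stage, and nicotine dependence will be balanced". In the primary-aim analysis, the one explicit mention of any of these is "Differences in treatment effects as a function of sex assigned at birth will also be examined", which is a separate question about effect modification. Disease progression returns only as an exploratory moderator under Secondary Aim 1.

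Under Power Considerations, "our power calculation assumes a sample size of 500 (250/500, 50% per group"), "we expect 5% abstinence in ST", and the target is a 7-point increase with 80% power from an unadjusted two-sided test of proportions.

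**The concern.** Given sound randomization, any baseline difference between the arms is a chance event. A significance screen on those differences therefore asks a question whose answer is already known, and it admits about one null variable in ten whether or not that variable predicts abstinence. A strong predictor that happens to be balanced stays out, and an irrelevant one that happens to be imbalanced goes in.

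The rule also works against the design. Stratification removes the imbalance that the screen looks for, so the three factors used to stratify are the ones it leaves out. If they are prognostic, leaving them out makes the standard error of the treatment effect somewhat larger than it need be.

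At stake are the pre-specification of the primary estimate and the match between design and analysis. The adjusted risk ratio is conditional on a covariate set that nobody can write down beforehand, and the analyst keeps discretion over which variables are tested and how they are coded.

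**Working it through.** **1. The plan's own figure.** Inputs from Power Considerations: n = 250 per arm, 5% in ST, 5% + 7 points = 12% in AT, two-sided alpha 0.05.
- Pooled rate = (0.05 + 0.12)/2 = 0.085; null SE = √(2 × 0.085 × 0.915/250) = 0.02494.
- Alternative SE = √((0.05 × 0.95 + 0.12 × 0.88)/250) = 0.02475.
- z = (0.07 − 1.96 × 0.02494)/0.02475 = 0.853, so power = 80.3%. The stated 80% reproduces. The unpooled form gives 80.7%.
- Expected abstainers: 250 × 0.05 + 250 × 0.12 = 12.5 + 30 = 42.5.

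**2. How often the screen selects by chance.** With m independent null variables, the expected number selected is 0.10m and the chance of at least one is 1 − 0.9^m.

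| m | Expected | At least one |
|---|---|---|
| 10 | 1.0 | 65% |
| 20 | 2.0 | 88% |
| 30 | 3.0 | 96% |

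The range is an assumption, because the article does not say which variables are screened.

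**3. Whether the stratification factors can be selected.** The article gives no block size, factor levels or prevalences, so these are assumed: permuted blocks of 4 or 8, and 8 strata (2 × 2 × 2).
- Bound for blocks of 4: each stratum can be out of balance by at most 2. One level of a factor spans 4 strata, so the arms can differ by at most 8 people in that level. For a level held by 30% of participants (150 of 500), the extreme case is 79 versus 71, a difference of 8/250 = 0.032. The SE is √(2 × 0.3 × 0.7/250) = 0.041, so z = 0.78. P<.10 needs 1.645.
- Simulation with N = 500: no stratification factor was selected in any of 4,000 trials at either block size, nor in 2,000 trials with 12 strata. Under unstratified allocation each was selected in about 10% of trials, and at least one of the three in 27%.

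**4. Consequence for the treatment test.** 1,500 simulated trials per scenario, with blocks of 4 within 8 strata, log-link Poisson with robust variance standing in for log-binomial, and ten further baseline variables. Assumed prognostic strengths on the log risk scale: −0.3, −0.3 and −0.7 for the stratification factors, and 0.3 per SD for three of the ten other variables.

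| Model | Power, 5% vs 12% | Null rejection, 8.5% abstinence | Null rejection, 5% abstinence |
|---|---|---|---|
| Unadjusted | 80.6% | 4.2% | 3.6% |
| P<.10 rule | 80.7% | 4.5% | 3.5% |
| Group + three stratification factors | 81.5% | 4.5% | 3.7% |

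Monte Carlo error is about 1 point for power (√(0.8 × 0.2/1500) = 0.010) and 0.5 point for null rejection. The gain from the fixed set over the rule is 81.5 − 80.7 = 0.8 point. A separate run of 1,200 trials gave 80.6% and 81.5%, a paired difference of 0.9 point (SE 0.5), and mean standard errors of the log risk ratio of 0.335 (rule) and 0.331 (fixed set), about 1% apart.

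**The case against.** The strongest reply is that the rule does little damage. Several readings that a reader might infer go too far:

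- **Material loss of power.** Not supported. At the plan's own rates the gain from fixing the covariates is about 1 point and is hard to separate from simulation error.
- **A biased or invalid test.** Not supported. Null rejection does not exceed 5% under the rule. The screen uses baseline comparisons of the arms and not the outcome, so if applied as written it cannot be steered by the treatment effect.
- **A model overloaded with irrelevant variables.** Not shown. In the 1,200-trial run the rule selected 2.4 covariates on average, the log-binomial model converged every time, and the mean log risk ratio was essentially unchanged (0.912 versus 0.910). The fix itself adds three factors, so model size is not the complaint.
- **A near-certain count of chance selections.** Table 1 has 27 rows with a baseline tick, which would give 27 × 0.10 = 2.7 selections and a 1 − 0.9^27 = 94% chance of at least one. But the article does not say that all are screened, and measures of stress, affect and depression overlap, so independence fails. The 10-to-30 range is the fairer statement.
- **Stratification factors deliberately excluded.** The article nowhere says so, and a fuller document could enter them.

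All of these limits stand. What also stands is that the P<.10 rule is stated in the article for the primary model. It is a poor rule that has been fixed, not detail left to another document, and as stated it does not bring the stratification factors in.

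**Conclusion.** The concern holds in a limited form. The stated rule selects primary-model covariates on chance imbalance, leaves the adjusted risk ratio dependent on a set unknown until the data are seen, and will almost never admit the factors on which randomization was stratified.

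The weight of the point is pre-specification and agreement between design and analysis. The numerical effect is minor: about 1 point of power, about 1% in the standard error, and no type I error inflation. Those sizes rest on assumed prognostic strengths, block sizes and factor prevalences. With sparse strata or looser balancing, selection of a stratification factor could rise above zero, but should stay well below the 10% seen without stratification. The change is worth making because it is nearly free, not because the trial is endangered without it.

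**What to change.** In Primary Aim, delete the P<.10 rule and state that the primary log-binomial model contains treatment group plus sex assigned at birth, HIV disease stage and nicotine dependence, coded as in the randomization. Any further prognostic baseline covariate should be named before outcome data are examined. In the Data Analysis Plan, make the baseline group comparisons descriptive only. Report the unadjusted result as a sensitivity analysis; it also corresponds to the test on which the power calculation rests.

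The cost is a sentence or two. The stratification factors must be known before randomization, so no new data are needed, and the sample size stays at 500. There is one small downside: with about 42 expected abstainers, 12 to 13 of them in ST, the log-binomial fit may fail to converge. The plan should name a fallback in advance, such as Poisson regression with robust variance on the same covariates.

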### Recruitment and Screening

Participants will be recruited from Florida using web-based advertisements. As of 2018, 116,689 Floridians were living with HIV [44]. On the basis of national data suggesting that 32% to 42% of US adults with HIV currently smoke [2,3], we expect that about 39,675 will be current smokers. Thus, our recruitment goal of 500 participants should be achievable within the proposed 42-month recruitment period.

Web-based advertisements will describe the study and direct potential participants to a landing page, which will provide more information about the study. Interested participants will complete a short web-based prescreening questionnaire, and those who pass the prescreener will be automatically redirected to the study’s eligibility questionnaire. Those who do not complete the self-administered web-based screening form will be contacted by the study staff and offered screening over the phone. Individuals who are eligible and interested in participating in the study will provide informed consent electronically or verbally over the phone and receive a copy of the informed consent document via email or mail. They will then provide HIV status documentation via a REDCap link. Once the documentation is verified, participants will be asked to complete a baseline assessment. The full list of measures to be completed for each assessment is shown in Table 1.

**Table 1 table1:** Study measures and assessment schedule.

Measure	Assessment schedule				
	Baseline	Weekly	3-month	6-month	12-month
Demographics and smoking history [45,46]	✓				
Drug use history [47]	✓				
Alcohol history and follow-up [48]	✓		✓	✓	✓
Smoking status [49]		✓^a^	✓	✓	✓
Heaviness of smoking index [50]	✓				
Financial Strain Questionnaire [51]	✓		✓	✓	✓
Contemplation ladder [52]	✓	✓^a^	✓	✓	✓
Reasons for quitting (intrinsic and extrinsic motivation) [53]	✓				
Sense of control [54]	✓		✓	✓	✓
Self-efficacy Scale [55]	✓	✓^a^	✓	✓	✓
Perceived Stress Scale-4 [56]	✓	✓^a^	✓	✓	✓
Positive and Negative Affect Scale [57,58]	✓		✓	✓	✓
Patient Health Questionnaire-8 [59]	✓		✓	✓	✓
Client Satisfaction Questionnaire [60]			✓	✓	
Health utilities (EQ-5D-5L^b^) [61]	✓		✓	✓	✓
Antiretroviral therapy adherence [62]	✓		✓	✓	✓
HIV symptoms burden [63]	✓		✓	✓	✓
Brief Resilience Scale [64]	✓		✓	✓	✓
HIV stigma scale [65]	✓		✓	✓	✓
Clinical measures	✓				✓
USDA^c^ household food insecurity survey [66]	✓		✓	✓	✓
CDC^d^ healthy days core module [67,68]	✓		✓	✓	✓
Subjective social status [69]	✓		✓	✓	✓

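### Secondary Aim 2 states no baseline EQ-5D-5L adjustment for the QALY difference, so precision is lost and chance imbalance enters the point estimate

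*Protocol article*

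**What the plan says.** All of this is in the protocol article.

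- **ICER.** Secondary Aim 2 has it "calculated as the difference in mean costs between new (ie, AT) and ST divided by the difference in mean effectiveness between the two". The definition is general. It comes before the effectiveness measures are listed: quitters and years of life saved, and then "We will also include quality-adjusted life-years, which will be calculated based on a measure of health utilities, the EQ-5D-5L [61".
- **Time points.** The short-term analysis uses quitters and QALYs and will "assess cost-effectiveness based on information collected at the 3-, 6-, and 12-month follow-ups". Baseline is not mentioned there, but Table 1 schedules the EQ-5D-5L at baseline, 3, 6 and 12 months.
- **Uncertainty.** Point estimates come first, then: "To obtain the 95% CIs, we will apply nonparametric bootstrapping methods to the person-level data [129".
- **Covariates in the economic analysis.** These appear only in the net-benefit regression, which is placed last: "Individual-level net benefit will be regressed on covariates, plus a binary variable reflecting AT versus ST". The covariates are not named.
- **Baseline differences in general.** The Data Analysis Plan says: "The samples will be compared to identify differences despite randomization, which may necessitate inclusion in models testing hypotheses". The Primary Aim sets a P<.10 rule for covariates in the log-binomial model for abstinence.
- **Stratification.** Under Randomization: "Sex assigned at birth, HIV disease stage, and nicotine dependence will be balanced". Utility is not a stratification factor.

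**The concern.** Under the usual area-under-the-curve rule, baseline utility is itself part of a 12-month QALY, and it is normally correlated with each later utility. If the arms differ by chance at baseline, a plain difference in mean QALYs inherits a large share of that difference. The true QALY difference within 12 months is likely to be small if it arises mainly through extra quitters. A modest imbalance could then be as large as the effect, and the QALY ICER divides by that difference. The covariate that would remove this component is already collected before randomization, but no stated QALY analysis uses it. What is at stake is the precision of the QALY difference, and how far its point estimate can be read at face value.

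**Working it through.** **The plan's own figure.** The article gives no power or precision for QALYs. Its only figure is 80% power for 12% versus 5% abstinence with 250 per group (Power Considerations). The pooled rate is 0.085. The null SE is √(2×0.085×0.915/250) = 0.02494 and the alternative SE is √((0.05×0.95+0.12×0.88)/250) = 0.02475. Power = Φ((0.07−1.96×0.02494)/0.02475) = 80.3%. The figure reproduces, so the 7-point gain and 250 per arm are used below.

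**Assumptions (not in the article).** Utility SD 0.20 at each visit; equal correlation ρ between any two visits; trapezoid QALY over one year; complete follow-up; utility gain of 0.02 to 0.10 per extra quitter, held for the full year; no QALY gain by any other route.

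**Formulas.**
- Trapezoid weights at 0, 3, 6 and 12 months: 0.125, 0.25, 0.375, 0.25. The sum of squares is 0.28125.
- Carry-over of a baseline difference into the QALY difference: 0.125 + 0.875ρ.
- QALY variance in units of SD²: 0.28125 + 0.71875ρ.
- Share of variance removed by adjustment: r² = (0.125+0.875ρ)² / (0.28125+0.71875ρ).
- SE of the baseline difference: 0.20×√(2/250) = 0.0179.
- Assumed effect: 0.07×0.02 = 0.0014 to 0.07×0.10 = 0.0070 QALY.

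| ρ | Carry-over | Shift from 1-SE imbalance | r² | SE unadjusted | SE adjusted |
|---|---|---|---|---|---|
| 0.3 | 0.3875 | 0.0069 | 0.30 | 0.0126 | 0.0105 |
| 0.5 | 0.5625 | 0.0101 | 0.49 | 0.0143 | 0.0102 |
| 0.7 | 0.7375 | 0.0132 | 0.69 | 0.0158 | 0.0088 |

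A one-SE imbalance therefore moves the estimate by about the top of the assumed effect range or more.

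**Sensitivity.** With SD 0.10 to 0.25 and ρ 0.4 to 0.8, the one-SE shift runs from 0.004 to 0.018. The probability that the shift exceeds the effect in absolute size runs from 10% (SD 0.10, ρ 0.4, gain 0.10) to 94% (SD 0.25, ρ 0.8, gain 0.02). At SD 0.20, ρ 0.6 and gain 0.05 it is 76%. A simulation at that setting gave an SE of 0.0155 unadjusted and 0.0097 adjusted.

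**What adjustment does not achieve.** For an effect of 0.0070, two-sided power rises only from 7–9% to 10–13% over ρ 0.3 to 0.7. At ρ 0.5 the chance of a wrong-sign difference goes from 46% to 45% (effect 0.0014), 40% to 37% (0.0035) or 31% to 25% (0.0070).

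**Would an imbalance screen catch it?** Suppose the P<.10 rule were extended to QALYs. At SD 0.20 and ρ 0.5, an imbalance just below the trigger is 1.645×0.0179 = 0.029. It would shift the QALY difference by 0.5625×0.029 = 0.017, more than twice 0.0070, and no adjustment would follow.

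**The case against.** The ICER sentence is a textbook definition covering every effectiveness measure. It does not exclude adjusted means, and the follow-up times may only be evaluation horizons. A condensed article commonly leaves value sets, QALY rules and covariate lists to a fuller economic plan. The article also provides for adjustment: the imbalance rule could take in a health-related variable such as utility, and the net-benefit approach is adopted partly because it permits covariates. Much of this stands. A reader might infer that the plan chose a raw contrast and ruled out adjustment; the text does not say so. It remains true that neither provision names baseline utility, and neither is said to alter the deterministic or bootstrapped ICER.

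Three further inferences should be resisted:
- **Systematic bias.** Randomization makes the unadjusted difference unbiased, and the person-level bootstrap interval reflects chance imbalance. The cost is lost precision and a point estimate that depends on the imbalance observed.
- **A large gain in power.** An effect with 80% unadjusted power would have 92% to above 99% after adjustment. Such an effect is 2.802×SE = 0.035 to 0.044 QALY, at least five times the assumed maximum of 0.0070.
- **A distorted acceptability curve.** The Bayesian model behind the curve is described with binomial abstinence as its effectiveness outcome. No QALY curve is stated.

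**Conclusion.** The point holds as a low-severity improvement. As written, the QALY contrast has no stated adjustment for a baseline measure already collected. Under the assumptions above, adjustment would cut its variance by about 30% to 69% and remove an imbalance component of 0.007 to 0.013 QALY per SE, against an assumed effect of 0.0014 to 0.0070. These sizes rest on assumed SD, correlation and gain per quitter, and the comparison varies widely over plausible values. A reader might infer that adjustment would rescue the QALY result. It would not: the contrast stays imprecise and the wrong-sign risk falls by only a few points. The primary outcome and the quitter and years-of-life-saved ICERs are unaffected.

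**What to change.** In Secondary Aim 2:

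1. State that 12-month QALYs are the area under the baseline, 3-, 6- and 12-month EQ-5D-5L utilities.
2. Estimate the incremental QALY by regressing QALYs on arm and baseline utility. Use this estimate in the base-case QALY ICER and refit it in each bootstrap replicate.
3. Name baseline utility as a fixed covariate in the QALY-based net-benefit regression, whatever any imbalance test shows. Do the same for an acceptability curve only if one is built for QALYs.
4. Report the unadjusted mean difference descriptively.

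If a separate economic analysis plan exists, the wording can go there, before outcome data by arm are seen. The cost is a few sentences and one covariate, with no new data or visits and no change in sample size.
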